### Interventions

All participants, regardless of treatment group, receive 18 therapy sessions over 6 months. The frequency of sessions is the same across treatment groups: twice weekly in weeks 1 and 2, weekly for weeks 3 to 10, fortnightly for weeks 11 through 18, and every third week for weeks 19 to 24. In other words, dose and intensity of treatment are the same for CFT and PFT.

*Conjoint Family-Based Treatment (CFT)*. In CFT, the whole family is expected to attend treatment sessions. This includes the adolescent, both parents (for two-parent families), and siblings. Treatment progresses through three phases detailed in the treatment manual [9]. In the first phase (sessions 1–12), therapy is focused on the eating disorder and includes a family meal undertaken in session two. This phase is characterised by attempts to absolve the parents from the responsibility of causing the disorder, and by capitalising on the strengths of their parenting to facilitate their offspring’s nutritional rehabilitation. Families are encouraged to work out for themselves how best to restore their child’s weight, drawing on a combination of common-sense practices (i.e., FBT asks parents, “What would you be feeding your child now if s/he were underweight for a medical reason?” and cautions them against symptom accommodation) and the eating disorders expertise of the therapist. In Phase 1, the majority of weight restoration is accomplished. In Phase 2 (sessions 13–16), once weight restoration is nearing completion, parents are helped to transition eating and weight control back to the adolescent in a developmentally appropriate manner. The third phase (sessions 17–18) is initiated when the patient achieves a stable weight and self-starvation has abated. The central theme is the establishment of a healthy adolescent stage of development in all aspects of functioning, including the patient’s relationship with his or her parents. In CFT, the mental health clinician weighs the patient at the beginning of each session and spends approximately 10 minutes with the adolescent before bringing the rest of the family in for the remainder of the 50-minute session.

*Parent-Focused Treatment (PFT).* In PFT, treatment progresses through the same three phases as CFT [9], however the parents and adolescent are seen in separate sessions. Each appointment begins with the adolescent being seen by the clinical nurse consultant who weighs the adolescent, assesses medical stability as needed, and provides brief supportive counselling for up to 15 minutes. The nurse communicates the weight and any other pertinent information to the therapist who then sees the parents for 50 minutes. The focus and content of the parent sessions are the same as in CFT, but without direct interaction with the adolescent. The only direct contact between the therapist and adolescent is at the first session, when the therapist briefly introduces themselves, and at the end of the final session, when the therapist farewells the family. As noted above, there is no family meal in PFT. Siblings are not included in PFT treatment sessions but other caregivers involved in weight restoration can be included (e.g., grandparent). A study treatment manual was developed for PFT and a detailed description of PFT will soon be published [19].

### Treatment fidelity

Therapists participate in weekly clinical supervision either in-person or via teleconference with an expert FBT clinician (authors [name] and [name]) to review treatment progress and ensure adherence to the treatment protocol. All treatment sessions for which consent has been provided are audio recorded. Randomly selected recordings are reviewed by author [name] throughout the trial.

### Additional patient monitoring

Medical oversight is provided at an outpatient appointment with a paediatrician at a minimum of every five weeks. The decision to hospitalise patients is made by the paediatrician and clinical team according to the team’s eating disorders admission protocol. If a participant requires hospitalisation for ≤ 21 days during the treatment phase of the study, they return to their allocated therapeutic arm after discharge and complete the treatment course. Admissions to hospital longer than 21 consecutive days or a third admission during treatment results in exclusion from the study treatment phase. Such participants are offered continued treatment as recommended by the clinical team.

Referrals can be made to the team psychiatrist for assessment of mental status and management of co-morbid mental health conditions and psychiatric crises as required. Once treatment has commenced, psychotropic medication can be prescribed by the psychiatrist for comorbid conditions (e.g., depression, anxiety). If the condition is not pre-existing, the EDE [20] is administered prior to commencement of medication.

### Measures

The study assessment timeline is shown in Table 1. The assessments are part of routine care of all patients in FBT at the service. Face-to-face assessments are conducted at baseline, week 4, week 12, end of treatment (i.e., Week 24), and at 6 and 12 months post-treatment completion. Written questionnaires are completed at each of these face-to-face assessments and at fortnightly intervals during the first 12 weeks of treatment. As a token of appreciation and reimbursement for time and travel, parents and adolescents receive a $20 gift card for attending each assessment at mid-treatment, end-of-treatment and follow-up. Participants who complete all written questionnaires are entered into a yearly draw for a $100 gift card.

**Table 1 T1:** Study measures and time points

**Measure**	**Source**	**Baseline**	**Each treatment session**	**Week 1**	**Week 2**	**Week 4**	**Weeks 6, 8 & 10**	**Week 12**	**Week 24 (End of Treatment)**	**6mth & 12mth FU**
Weight	Adolescent	✓	✓			✓		✓	✓	✓
Height	Adolescent	✓						✓	✓	✓
Menstrual status	Adolescent	✓	✓					✓	✓	✓
Binge/purge frequency	Adolescent	✓	✓			✓		✓	✓	✓
Eating Disorder Examination	Adolescent	✓						✓	✓	✓
	Parent	✓						✓	✓	✓
Mini International Neuropsychiatric Interview	Adolescent	✓							✓	✓
	Parent	✓							✓	✓
Children’s Yale-Brown Obsessive Compulsive Scale	Adolescent	✓				✓		✓	✓	✓
Yale-Brown-Cornell Eating Disorder Scale	Adolescent	✓				✓		✓	✓	✓
Five Minute Speech Sample	Parent	✓				✓		✓	✓	✓
Symptom Checklist-90-R	Parent	✓								
Family Environment Scale	Adolescent	✓			✓	✓	✓	✓	✓	✓
	Parent	✓			✓	✓	✓	✓	✓	✓
Borderline Personality Questionnaire	Adolescent	✓						✓	✓	✓
Children’s Depression Inventory	Adolescent	✓			✓	✓	✓	✓	✓	✓
Rosenberg Self-Esteem Scale	Adolescent	✓			✓	✓	✓	✓	✓	✓
Eating Disorders Examination-Questionnaire	Adolescent	✓			✓	✓	✓	✓	✓	✓
Positive and Negative Affect Scale	Adolescent	✓			✓	✓	✓	✓	✓	✓
	Parent	✓			✓	✓	✓	✓	✓	✓
Parents Versus Anorexia Scale	Parent	✓			✓	✓	✓	✓	✓	✓
Therapy Suitability and Patient Expectancy	Adolescent			✓	✓	✓	✓	✓	✓	
	Parent			✓	✓	✓	✓	✓	✓	
Helping Relationship Questionnaire	Adolescent				✓	✓	✓	✓	✓	
	Parent				✓	✓	✓	✓	✓	

*Eating Disorder Examination (EDE)*[21]. The EDE is a semi-structured interview used to diagnose eating disorders. It measures eating-related attitudes, cognitions, and behaviours primarily during the past 28 days. The EDE yields four subscale scores (Restraint, Eating Concern, Weight Concern, and Shape Concern) and a global score measuring the overall severity of eating disorder psychopathology. Behavioural symptoms of eating disorders (e.g., binge eating, purging) are assessed through a series of diagnostic questions about the frequency of behaviours in the 3–6 months prior to assessment. The EDE has good reliability and validity [22] and has been used in several studies of paediatric eating disorders [8,23].

A parent-report version (PEDE) is also utilised in this study [24,25]. Findings from the EDE and PEDE are integrated with the psychiatrist’s assessment to arrive at the diagnosis at baseline.

*Expected Body Weight (% EBW).* This is calculated as [current BMI]/[50^th^ percentile BMI] × 100. The 50^th^ percentile BMI is determined using the Centers for Disease Control charts relative to gender and age to the closest 6 months [17]. Weight is measured to the nearest 0.05 kg using regularly calibrated digital scales. A trained researcher weighs the adolescent in a gown, and the therapist/nurse weighs the adolescent in light indoor clothing without shoes. Height is measured to the nearest 0.1 cm using a wall mounted stadiometer. A trained researcher measures the adolescent’s height without shoes using a standard protocol.

*Binge/Purge Frequency.* Binge eating and purging episodes in the previous week are assessed by self-report at each treatment session and each assessment time point.

*Mini International Neuropsychiatric Interview for Children and Adolescents (MINI-Kid)*[26]. The MINI-Kid is a structured clinical interview for assessment of DSM-IV psychiatric disorders in children and adolescents. The MINI-Kid has been shown to be a reliable and valid assessment of psychiatric disorders [27,28]. The results of the MINI-Kid self-report and parent-report versions are integrated with the psychiatrist’s assessment to arrive at a final diagnosis at baseline.

*Children’s Yale-Brown Obsessive Compulsive Scale (CY-BOCS)*[29]. The CY-BOCS is a semi-structured interview designed to assess the presence and severity of obsessions and compulsions in children. The CY-BOCS was modified for children from the adult Yale-Brown Obsessive Compulsive Scale (Y-BOCS) [30]. The CY-BOCS has been shown to have high internal consistency as well as good convergent and divergent validity [29].

*Yale-Brown-Cornell Eating Disorder Scale (YBC-EDS)*[31]*.* Based on the Y-BOCS, the YBC-EDS is designed to assess the presence and severity of obsessions and compulsions related to eating behaviours, weight, and exercise. Studies of patients with eating disorders have demonstrated the YBC-EDS has good reliability and validity, and is sensitive to change over the course of therapy [31,32].

*Five Minute Speech Sample (FMSS)*[33]. The FMSS was developed as a brief measure of expressed emotion in family members of individuals with a psychiatric illness. The parent is asked to speak for 5 minutes about their child and the content is coded by trained assessors. Content is rated as either high or low in expressed emotion based on level of criticism and emotional over-involvement displayed during the speech sample. In studies of relatives of individuals with schizophrenia [33,34] and individuals with AN [35], the FMSS has been shown to be comparable to the Camberwell Family Interview [36], a 1–2 hour long semi-structured interview considered the gold standard for assessing expressed emotion.

*Symptom Checklist-90-R (SCL-90-R)*[37]*.* The SCL-90-R is a 90-item self-report measure of psychiatric symptomatology including depression, anxiety, obsessive-compulsive, and psychotic symptoms. The respondent indicates the degree to which they have been distressed by each symptom during the preceding week. Studies have shown the SCL-90-R to have good internal consistency and to be a valid measure of general psychiatric distress [38,39].

*Family Environment Scale (FES)*[40]*.* The 27-item relationship dimension of the FES is used to assess the degree of cohesion, expressiveness, and conflict in the family. This scale has been used in numerous studies to assess family functioning including studies of eating disorder symptomatology [41]. The FES has been shown to have good internal consistency, to correlate with other measures of family environment, and to change with family-focused interventions [40].

*Borderline Personality Questionnaire (BPQ)*[42]*.* The BPQ is an 80 item, self-report measure of borderline personality traits as defined by the DSM-IV (e.g. affective instability, impulsivity, self-harm, fear of abandonment, relationship difficulties, and identity issues). This questionnaire has been shown to have good internal consistency and validity [42,43]. In a sample of Australian adolescents, the BPQ was found to have high internal consistency, diagnostic accuracy, high test-retest reliability, and moderate sensitivity [44].

*Children’s Depression Inventory (CDI)*[45]. The CDI is a 27-item self-report measure of depressive symptomatology experienced by children and adolescents in the past 2 weeks. Studies have shown the CDI to have high internal consistency and to be a valid measure of overall level of depressive symptomatology in children and adolescents [46,47]. The suicidal ideation item is not included in this study.

*Rosenberg Self-Esteem Scale (RSE)*[48]*.* The RSE is a widely used self-report instrument of 10 items measuring an individual’s overall self-esteem. A meta-analysis of 23 factor analytic studies including 32,491 participants found support for a one-factor model of self-esteem as measured by the RSE [49].

*Eating Disorders Examination-Questionnaire (EDE-Q)*[50]*.* The EDE-Q is a self-report measure adapted from the EDE. Only the 5-item Dietary Restraint subscale is used in this study to assess attempts to restrict dietary intake. The EDE-Q Restraint Scale has high internal consistency [51] and results are highly comparable to those assessed using the EDE interview [52].

*Positive and Negative Affect Scale (PANAS)*[53,54]. The PANAS is a self-report measure of positive and negative affect. The respondent is presented with a list of feelings (e.g., sad, happy, irritable) and ask to indicate to what extent they felt that way in the past 2 weeks. It is a well validated, reliable and widely used measure of emotional experience for use with both adults and children [53,54]. The current study utilises 41 items from the PANAS Expanded Form [53] to derive Positive Affect and Negative Affect scales as well as the Fear, Hostility, Guilt, Sadness and Joviality subscales. Adolescents report on their own emotional experience and parents report on their observations of their child’s emotional expression.

*Parents Versus Anorexia Scale (PVA)*[55]. This is a 7-item measure of self-efficacy of parents in FBT; that is, parents’ perceptions of their ability to bring about recovery in their child [55]. The measure was designed to align with the principles of FBT outlined in the manual [9]. The PVA has been found to have acceptable internal consistency and to be positively correlated with total increase in % EBW during FBT [55].

*Therapy Suitability and Patient Expectancy*[56]*.* Parent and adolescent perception of the suitability of the treatment is assessed with the question “How suitable do you think this therapy is for your problem?” Their expectation of improvement with treatment is assessed with the question “How successful do you think therapy will be?” Each item is rated on an 11-point scale (0 = *Not at all*, 10 = *Extremely*). The questions were adapted from those used in a trial of FBT for bulimia nervosa [56].

*Helping Relationship Questionnaire (HRQ)*[57]. The HRQ measures two main aspects of the therapeutic relationship: the experience of being helped and supported, and the experience of being in a collaborative effort with the therapist. Eleven items are rated on a 6-point scale (-3 = *Strongly feel it’s true*, +3 *Strongly feels it’s untrue*). Two additional open-ended questions ask the respondent to comment on the ways they feel improved and the ways they feel worse, and a final item asks the respondent to rate their improvement so far (1 = *Not at all*, 5 = *Very much*). The HRQ has been used in a trial of FBT for bulimia nervosa [56].

### Primary outcome

The primary outcome is full remission, defined as ≥ 95% EBW and an EDE Global score within one standard deviation of community norms.

### Secondary outcomes

The secondary outcomes are partial remission (defined as ≥ 85% EBW) and changes in eating pathology (EDE subscales and behaviour frequency scores), depressive symptoms (CDI) and self-esteem (RSE).

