### Aims and hypotheses

The aims of this study are to:

1. Examine the relative benefits of PFT compared to CFT in a randomised controlled trial with a cohort of outpatients with AN and EDNOS- Anorexia Nervosa type (EDNOS-AN);

2. Explore predictors and moderators of treatment response; and

3. Explore mediators of treatment response.

It is hypothesised that:

1. PFT will be more effective than CFT as indicated by more participants achieving full remission and partial remission after 6 months of treatment and at 6 and 12 months follow-up;

2. Adolescents with parents who are highly critical and are assigned to PFT will have better outcomes compared to adolescents with parents who are highly critical and are assigned to CFT;

3. Regardless of treatment assignment, outcomes will be poorer for adolescents with co-morbid psychiatric illness, high levels of obsessionality, features of personality disturbance, parent psychopathology, high levels of parental criticism, poor therapeutic relationship, and/or low expectation for treatment effectiveness. These factors will also be explored as potential moderators of outcomes with respect to treatment assignment;

4. Treatment response will be mediated by reduced dietary restraint and depressive symptomatology, and increased self-esteem, parent efficacy and family functioning.

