### Inclusion criteria

Participants are eligible to participate if they are aged between 12 to 18 years, meet DSM-IV criteria for AN (excluding the amenorrhea criterion) or EDNOS-AN [16], are sufficiently medically stable for outpatient treatment, and are living with at least one parent or guardian who can read and speak English to at least a sixth-grade level. DSM-IV criteria were applied as the trial commenced prior to publication of the DSM-5 [1]. In anticipation of the DSM-5 criteria, however, the amenorrhea criterion was excluded and, in the absence of explicit acknowledgement of fear of weight gain or becoming fat, persistent behaviours that interfere with weight gain are considered diagnostic. Weight thresholds are ≤85% EBW for AN and 85-90% EBW for EDNOS-AN. For adolescents at or above the 75^th^ percentile for height, the weight threshold was set higher (≤95% EBW). EBW is calculated from median body mass index for age and gender using the Centers for Disease Control charts [17]. Medical stability is determined by a paediatrician or nurse according to a standard protocol that was informed by published guidelines [18].

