### Randomisation

A statistician independent of the research group generated a randomisation schedule using block randomisation with variable block sizes (currently masked from research personnel). Randomisation is stratified by eating disorder severity (low vs. high) to ensure equal allocation to each of the treatment arms. High severity is defined as <80% EBW, illness duration >12 months, and the presence of one other psychiatric diagnosis (i.e., all three criteria must be met). The randomisation schedule is only accessible by designated staff members at the Royal Children’s Hospital who are independent of the Eating Disorders Program team including the research team. When randomisation is required, a researcher sends an email with the participant identification number and severity category to one of the independent staff members requesting randomisation. The allocation is sent via reply email and the researcher communicates the allocation to the family and treating clinicians.

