### Data analysis

Remission will be determined separately at post-treatment and follow-up. The primary outcome analysis will be based upon intent-to-treat. In those cases in which there are missing post-treatment or follow-up data, the pre-treatment observation will be carried forward to characterise that participant’s response [58]. Groups will be compared on remission at post-treatment and follow-up using two-tailed Fisher’s Exact test with *alpha* set to .05. The secondary outcome category is the proportion of participants partially remitted. CFT and PFT will be compared at post-treatment and follow-up using Fisher’s Exact test.

A secondary analysis will be performed using a mixed effects linear regression model [59] to compare CFT and PFT participants on eating pathology, depression and self-esteem at mid-treatment (week 12), end-of-treatment (week 24), 6-month follow-up, and 12-month follow-up controlling for pre-treatment levels. Analyses will be performed on log-transformed variables for behavioural frequencies to satisfy the assumptions for the linear model. Random regression models allow for the inclusion of individuals with missing data. Consequently, no data imputation will be performed. Comparisons between groups will be based upon the main effect for group with a two-tailed alpha of .05. *Post hoc* comparisons between groups at specific time-points will be based upon a two-tailed Bonferroni corrected *Post hoc* comparisons between groups at specific time-points will be based upon a two-tailed Bonferroni corrected *alpha* of .0125 (.05/4).

Moderation analyses will be performed using logistic regression analyses, with models using main effects for treatment, moderator, and treatment-by-moderator analyses to predict remission at post-treatment and follow-up assessments. Bootstrap mediation analyses with bias-corrected confidence intervals will be performed using the *PROCESS* macro developed by Hayes [60].

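### Partial remission (≥85% EBW) is already met at enrolment by part of the eligible population, so the raw proportions overstate response and may dilute the arm comparison

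*Protocol article*

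**What the plan says.** Under Secondary outcomes, the protocol article gives a weight-only definition at a fixed threshold: "partial remission (defined as ≥ 85% EBW". Full remission, under Primary outcome, needs a higher weight and also an EDE Global criterion.

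Under Inclusion criteria: "Weight thresholds are ≤85% EBW for AN and 85-90% EBW for EDNOS-AN". For adolescents at or above the 75th height percentile, "the weight threshold was set higher (≤95% EBW".

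Hypothesis 1, under Aims and hypotheses, expects PFT to be superior through "more participants achieving full remission and partial remission after 6 months of treatment and at 6 and 12 months follow-up". Partial remission is thus one of its two indicators at each time point.

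Under Data analysis: "The secondary outcome category is the proportion of participants partially remitted". The arms are compared by Fisher's Exact test, with no restriction to participants below the threshold at entry and no baseline adjustment. For missing outcomes, in the text on the primary analysis, "the pre-treatment observation will be carried forward".

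Under Randomisation, the stratification factor is severity: "High severity is defined as <80% EBW, illness duration >12 months, and the presence of one other psychiatric diagnosis". All three conditions must hold.

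**The concern.** The entry range and the success threshold overlap. A participant who starts at or above 85% EBW is classed as partially remitted on the day of randomisation and can afterwards only keep or lose that status. Someone who enters at 88% and ends at 86% has lost weight but counts as a success.

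The carry-forward rule may add to this. It usually classes a dropout as a non-responder. If it is applied to partial remission, a dropout who entered at ≥85% becomes a success.

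Two things are at stake. The reported proportions would be read as response rates, and they are too high for that. The arm difference may also be pulled towards zero, which weakens one of the two indicators of hypothesis 1.

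**Working it through.** **1. The thresholds side by side**

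| Entry route | Entry %EBW | Already ≥85% at entry? |
|---|---|---|
| AN | ≤85 | only at exactly 85 |
| EDNOS-AN | 85-90 | all |
| Height ≥75th percentile | up to 95 | those entering at 85-95 |

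This step needs no assumption. Nothing else in the article removes the overlap.

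**2. The plan's own figure**

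The plan gives no sample size for partial remission. Its only calculation is for remission: 45 per group for a 27-point difference, two-sided .05, 80% power. With a control rate of about 50% (Discussion), the unpooled formula gives (1.960 + 0.842)² × (0.50×0.50 + 0.77×0.23) / 0.27² = 46.0 per group, close to 45. Dropout: 45 / 0.90 = 50. I use 50 per arm below.

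**3. Size of the effect on partial remission**

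Assumed, because the documents do not give them:
- q, the share starting at ≥85% EBW: 20%, 30% or 40%.
- Partial remission in those starting below 85%: 60% CFT, 85% PFT.
- Retention r, the proportion of those starting at ≥85% who are still there: two scenarios.

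Formula for each arm: p(arm) = q × r(arm) + (1 − q) × p(arm, below 85%). Power is for the two-sided Fisher test at .05, by full enumeration. With q = 0 the difference is 25 points and power is 75.8%.

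Scenario A: retention 97% in both arms, so no treatment effect in those starting at ≥85%. Example at q = 20%: CFT 0.2×0.97 + 0.8×0.60 = 0.674; PFT 0.2×0.97 + 0.8×0.85 = 0.874.

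| q | CFT | PFT | Difference (points) | Power, 50 per arm |
|---|---|---|---|---|
| 20% | 67.4% | 87.4% | 20.0 | 60% |
| 30% | 71.1% | 88.6% | 17.5 | 51% |
| 40% | 74.8% | 89.8% | 15.0 | 41% |

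Scenario B: retention 80% CFT, 97% PFT. Example at q = 20%: CFT 0.2×0.80 + 0.8×0.60 = 0.640; PFT unchanged at 0.874.

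| q | CFT | PFT | Difference (points) | Power, 50 per arm |
|---|---|---|---|---|
| 20% | 64.0% | 87.4% | 23.4 | 73% |
| 30% | 66.0% | 88.6% | 22.6 | 72% |
| 40% | 68.0% | 89.8% | 21.8 | 71% |

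**4. Comparison restricted to those below 85% at baseline**

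With 50 × (1 − q) per arm, that is 40, 35 or 30, and 60% v 85%, power is 64.1%, 56.5% or 48.9%. This beats Scenario A at every q and falls short of Scenario B at every q.

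**5. A second set of rates**

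With 50% v 77% below the threshold and 100% retention in both arms, the 27-point difference becomes 27 × 0.8 = 21.6 points at q = 20% and 27 × 0.6 = 16.2 at q = 40%. Power falls from 75% to 60% and 42%. The pattern of Scenario A does not hinge on the 60% and 85% chosen.

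**The case against.** A reader might infer that the outcome does not measure response at all. The documents do not support that. For anyone entering below 85% EBW, crossing the threshold is weight gain, and for those entering above it, falling below is a meaningful deterioration. The outcome is diluted, not void.

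A reader might also take the power loss as certain. It follows from setting retention equal in both arms. Scenario B shows that with better retention under PFT most of the power survives. The protocol says nothing about retention, so the dilution is a conditional result.

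The strongest defence is that the outcome is secondary and the trial was sized on remission. The comparison is between randomised arms, so the overlap does not inflate the type I error. Under Scenario A it works against the trial's own hypothesis. All of this stands, and it lowers the severity. It does not answer the point about raw proportions, which count unchanged and mildly worsened participants as successes in both arms.

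On the remedy, it can fairly be said that restriction leaves the full randomised sample, uses fewer participants, ignores deterioration, and gains power only under Scenario A. Restricting on a baseline variable does keep the comparison randomised. However, the severity strata do not balance status at 85% EBW, so the numbers per arm could differ by chance. An adjusted analysis of everyone is therefore a legitimate alternative.

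**Conclusion.** The point holds as a defect of a secondary outcome and should be fixed. That some eligible participants meet partial remission at enrolment follows directly from the two sets of thresholds. That the raw proportions overstate response follows whenever retention in this group exceeds the response rate in the rest. In the scenarios above, the CFT figure rises from 60% to between 64% and 75% with no added benefit.

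The loss of power is less certain. It runs from 76% down to 60-41% if treatment has little effect in those starting at ≥85%, and only to 73-71% if retention is 80% v 97%. Both ranges rest on an assumed share of 20-40%. Use of the carry-forward rule for this outcome is likely but not stated, because the rule stands beside the primary analysis.

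A reader might infer that the primary outcome has the same flaw, since the tall-participant entry limit and the weight part of full remission share the value 95%. The documents do not support that: only a tall participant at exactly 95% is affected, and full remission also needs the EDE criterion.

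**What to change.** Reconcile the entry range with the definition of partial remission so that baseline status alone cannot count as success. The clinical threshold itself is for the investigators. Either of these would do:

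- Report partial remission by baseline status (<85% v ≥85% EBW), with the arm comparison in those below 85% at baseline as the measure of response. Show the others as having kept or lost the status.
- Keep all participants and adjust the comparison for baseline %EBW status, for example with a stratified test, and still show the proportions by baseline status.

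State whether carry-forward applies to this outcome and, if so, that a participant at ≥85% at entry with missing data is not thereby a success.

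Also add %EBW as a continuous outcome, adjusted for baseline %EBW, to the planned mixed model at week 12, week 24 and the 6- and 12-month follow-ups. Table 1 schedules both weight and height at these points. Week 4 has weight but no height, and the planned model does not use it.

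The cost is the wording of one endpoint and one further model on data already collected. The downside of the restricted comparison is a smaller sample (40, 35 or 30 per arm at the assumed shares), and it is not always more powerful. The choice should be fixed before outcome data are compared by arm.
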